### Interventions

Both study groups reflect current processes within existing clinics at the participating hospitals.

### VFC (intervention group)

Patients randomised to the VFC (intervention) group will be contacted via phone and email to organise an initial follow-up with a physiotherapist; usually within 5 days after their referral is received. Patients are sent an email with their appointment details and a fracture management fact sheet. The fact sheet explains their clinical condition, expected recovery, early rehabilitation exercises, activity limitations and information on care escalation. These fact sheets were adapted with permission from Royal Melbourne Hospital’s VFC.

All patients are offered a video consultation with a physiotherapist unless they choose to have their review via phone. During the virtual consults, the physiotherapist conducts an assessment, discusses the X-ray findings and provides a management plan. The virtual consult sessions are usually approximately 30 min. An email summary of the consultation and follow-up appointment details are sent to the patient after the consultation. A Physitrack link may also be included in this email. Physitrack or PhysiApp is an internet-based programme that allows patients to view videos of their prescribed exercises. Patients are usually offered a follow-up virtual appointment at 2 weeks and 6 weeks post-fracture, or based on clinical need. Patients can contact the physiotherapist out of session if they have any concerns during their care period. Most patients are discharged from the VFC at 6 weeks post-fracture if there are no concerns. Patients will be supported with an interpreter, Aboriginal Cultural Support Team or with loaned devices and data as required. For example, although many older patients (aged 60+) currently use the virtual service, a digital patient navigator can assist patients and provide a smart phone with data so they can attend their virtual clinic appointments. We will monitor patient adherence by the number of consults attended; and the number of ad hoc patient contacts via phone or email with the clinic.

### In-person fracture clinic (control group)

Patients randomised to the in-person fracture clinic will be contacted via phone or email to provide a follow-up appointment. Appointments usually occur 7–10 days after the referral is received, based on the availability of the on-call orthopaedic doctor. Clinical management and subsequent follow-ups of the control group will be determined by the orthopaedic doctors at the in-person fracture clinic. Clinical management can include a physical assessment by a doctor, radiology scan, advice and exercises. A physiotherapist may be involved in the patient’s care. Patients in the control group may receive written instructions about their recovery and exercises as per current processes. The in-person consult sessions are usually approximately 20 min. Current practice suggests that patients may attend the in-person fracture clinic once or twice within 6 weeks post-fracture. We will monitor patient adherence by the number of consults attended.

Staff providing care to study participants will be trained on the trial protocol and be regularly supported by study investigators to ensure adherence to study protocol.

### Outcomes

The primary outcome of this study will be the participant’s physical function assessed using the PSFS at 12 weeks. This self-reported tool has shown to be sensitive to change in patients with musculoskeletal problems, including simple fractures.^13–15^ Participants list up to five functional tasks at baseline and score their level of ability — 0 (unable to perform activity) to 10 (able to perform activity at the same level as before the injury). Scores for each activity will be summed and calculated as an average of the total possible score for the participant (determined by the number of identified activities). We will compare the PSFS average scores between groups at 12 weeks as our primary measure. Table 1 summarises the outcome measures for this study.

**Table 1 T1:** Outcome measures

Milestones	Baseline	6 weeks	12 weeks
Patient characteristics	✓		
Patient-Specific Functional Scale	✓	✓	✓
EuroQol 5D-5L	✓		✓
Pain Numerical Rating Scale	✓	✓	✓
Generic Short Patient Experiences Questionnaire		✓	
Health costs			✓
Healthcare utilisation			✓
Medication use		✓	
Adverse events and serious adverse events		✓	✓
Emergency department representations			✓
Patients requiring surgery			✓

EuroQol-5D-5L, EuroQol 5 Dimensions 5 Levels.

Secondary measures for this study will include:

Health-related quality of life measure assessed using the EuroQol 5 Dimensions 5 Levels (EQ-5D-5L) at baseline and 12 weeks.^16^Patient-reported experience measure assessed using the Generic Short Patient Experiences Questionnaire (GS-PEQ) at 6 weeks.^17^Pain assessed using the 0–10 Numerical Rating Scale at baseline, 6 and 12 weeks.^18^Cost borne by the healthcare service, measured at 12 weeks. We will collect data from the electronic medical records (eMR), SLHD Targeted Activity and Reporting System App Dashboard, and the hospital’s performance, data and finance departments to obtain the healthcare appointment duration, healthcare provider’s hourly rate, any health services utilisation and corresponding cost (including but not limited to outpatient, inpatient, ED, pharmacy, radiology, pathology and primary care), any infrastructure setup and maintenance cost, managerial and administrative overhead.Cost borne by patients, measured through the patient survey designed specifically for this study at 12 weeks.Healthcare utilisation assessed using a survey designed specifically for this study at 12 weeks. The survey will collect the number of other healthcare appointments for management of their injury. We will also ascertain if the patients used any other healthcare services through the patient’s eMR.Medication use assessed using a survey designed specifically for this study to assess the name and dose of prescription or over-the-counter medication for their injury at 6 weeks.Adverse events and serious adverse events assessed using a survey designed specifically for this study at 6 and 12 weeks. We will also collect data from safety reports within the eMR, and the NSW Health Incident Management System.ED representations measured by reviewing the eMRs at 12 weeks. This information may also be reported in the healthcare utilisation survey and the adverse/serious adverse event survey.Number of patients requiring surgery measured by reviewing the eMRs at 12 weeks. This information may also be reported in the healthcare utilisation survey and the adverse/serious adverse event survey.

### Sample size

A total sample of 312 participants will provide 90% power to detect a non-inferiority margin of 0.7 points on the 11-point PSFS with a 10% loss to follow-up, an SD of 2.0, α of 5% and a correlation score between baseline and final scores of 0.5 at 12 weeks.^19^ A negative between-group difference of ≤0.7 points will indicate that the VFC clinic is non-inferior to the in-person fracture clinic.

We chose an SD of 2.0 as this is between the mean value of the SD for the PSFS at follow-up in published studies that range from 1.7,^20^ 2.1^21^ and 2.2.^13^ The minimal important difference (MID) for the PSFS ranges from 1.3 (small change) to 2.7 (large change).^21 22^ Guidelines suggest using a non-inferiority margin of 50% (or less preferably) of the treatment effect of standard care versus placebo.^23^ Thus, we chose a between-group non-inferiority margin of 0.7 (50% of the MID of 1.3).

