### Primary analysis

Non-inferiority trials assess whether an intervention outcome is not clinically worse than a control. The PSFS score at 12 weeks post-randomisation is the primary outcome in this study and we have prospectively defined a non-inferiority margin (ΔT) of −0.7 points, which is the maximum difference we are prepared to tolerate and still consider virtual care not to be clinically inferior to in-person care. The null hypothesis is, therefore, that a difference of greater than ΔT exists in favour of in-person care (H0: Δ ≤−ΔT). This will be assessed by creating a 95% CI, which should be entirely above the non-inferiority margin for the intervention to be declared non-inferior. The PSFS score will be compared between treatment groups as the dependent variable in a generalised linear regression model for the primary analysis adjusting for baseline PSFS variables. The treatment difference will be based on the estimate of adjusted means and 95% CIs.

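### The non-inferiority margin of 0.7 is given as 50% of an MID of 1.3, but 50% of 1.3 is 0.65, and the guideline cited for it concerns a quantity the protocol does not report

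*Protocol article*

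**What the plan says.** The protocol article, Sample size, builds the margin in three steps.

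- It gives a range for the MID: "The minimal important difference (MID) for the PSFS ranges from 1.3 (small change) to 2.7 (large change").
- It cites a rule: "Guidelines suggest using a non-inferiority margin of 50% (or less preferably) of the treatment effect of standard care versus placebo".
- It concludes: "Thus, we chose a between-group non-inferiority margin of 0.7 (50% of the MID of 1.3").

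The same section sizes the trial on this value: "A total sample of 312 participants will provide 90% power to detect a non-inferiority margin of 0.7 points on the 11-point PSFS". The other inputs are 10% loss to follow-up, an SD of 2.0, α of 5% and a baseline-to-final correlation of 0.5.

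Primary analysis makes it the decision threshold: "we have prospectively defined a non-inferiority margin (ΔT) of −0.7 points", described as the value "which is the maximum difference we are prepared to tolerate and still consider virtual care not to be clinically inferior to in-person care". Non-inferiority is declared if the 95% CI lies wholly above that threshold. The model adjusts for baseline PSFS.

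**The concern.** The margin decides what this trial may conclude, so its stated origin should be correct. Two things in the derivation are not.

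First, the figure and its explanation disagree. A margin of 0.7 is not 50% of 1.3. The article introduces 50% as an upper value, with less preferred, yet the rounding goes up. Nothing tells the reader that any rounding took place.

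Second, the concluding sentence does not follow from the one before it. The guideline rule is a fraction of what standard care achieves over placebo. An MID measures what matters to patients and does not estimate the benefit of in-person care. Taking half of an MID can support a judgement of clinical acceptability. It cannot show that half of the standard-care effect is preserved.

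At stake is how a borderline result would be defended. If the lower confidence limit fell between -0.70 and -0.65, the trial would claim non-inferiority under its stated threshold, but the claim would fail against the half-MID that the text says the threshold represents.

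**Working it through.** **Inputs** (Sample size, unless noted): margin 0.7; MID 1.3 (smallest) to 2.7; SD 2.0; correlation 0.5; power 90%; α 5%, sidedness not stated there; loss 10%; equal groups (Eligibility criteria); decision by 95% CI with baseline adjustment (Primary analysis). Assumption not stated in the article: a true difference of 0.

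**1. The margin**

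- 0.5 × 1.3 = 0.65.
- 0.7 / 1.3 = 0.538, or 53.8%.
- If 1.3 is itself rounded, from somewhere between 1.25 and 1.35, half of it lies between 0.625 and 0.675, still below 0.7.
- For 0.7 to be exactly half, the MID would have to be 0.7 / 0.5 = 1.4.
- To one decimal, 0.65 rounds up to 0.7. Rounding down to 0.6 would give 0.6 / 1.3 = 46.2%, which stays within 50%.

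**2. Reproducing the stated 312**

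n per arm = 2 × SD² × (z for α + z for power)² / margin².

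With one-sided α of 5% and SD 2.0 without reduction for the correlation: 2 × 4 × (1.645 + 1.282)² / 0.49 = 139.8, so 140 per arm and 280 in total. Then 280 / 0.9 = 311.1, which rounds up to 312. The stated figure is reproduced with the margin of 0.7.

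**3. Power of the same 312 at 0.65**

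312 × 0.9 = 280.8, so 140 analysed per arm. Power = Φ(margin / SE − z for α). Two bases are shown because the formula that yields 312 differs from the analysis described under Primary analysis.

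| Basis | SE | Power at 0.7 | Power at 0.65 |
|---|---|---|---|
| One-sided 5%, SD 2.0 (reproduces 312) | √(2 × 4 / 140) = 0.239 | 90.0% | 85.9% |
| Two-sided 95% CI, baseline-adjusted SD 2 × √(1 − 0.5²) = 1.732 | √(2 × 3 / 140) = 0.207 | 92.2% | 88.1% |

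For example, on the second basis at 0.65: Φ(0.65 / 0.207 − 1.96) = Φ(1.18) = 0.881.

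**4. Size needed to hold 90% power at 0.65**

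- One-sided 5%, SD 2.0: 163 per arm, 326 analysed; 326 / 0.9 = 362.2, so 363 (364 if arms are equal).
- Two-sided 95% CI, adjusted: 150 per arm, 300 analysed; 300 / 0.9 = 333.3, so 334.

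**5. The guideline**

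The rule needs the effect of standard care versus placebo. The article contains no estimate of it. Neither 0.7 nor 0.65 can therefore be checked against the rule.

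**The case against.** The best defence is that this is a one-decimal rounding. The excess is 0.05 points on a 0–10 scale, about a quarter of the adjusted standard error (0.05 / 0.207 = 0.24). The authors started from the smallest MID in their range. The value 0.7 is used consistently in the power statement and in the decision rule, so two analysts would reach the same conclusion from the same data. Primary analysis already describes 0.7 as the largest tolerable difference, which is a clinical-acceptability argument. Recruitment had begun, and holding 90% power at 0.65 would need more than 312 patients. All of this stands and lowers the weight of the point. It does not make the parenthesis correct, and it does not supply the standard-care effect from which the margin is said to follow.

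Three stronger readings are tempting, and the document supports none of them.

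- A reader might infer that the margin breaks the guideline's 50% ceiling. That ceiling applies to the effect of standard care versus placebo, which is not given, so a breach cannot be shown. What can be shown is that 0.7 exceeds the article's own half-MID derivation.
- A reader might infer an inflated error rate. If the true deficit were 0.65, the chance of claiming non-inferiority against 0.7 would be Φ(0.05 / 0.207 − 1.96) = 4.3%. A true value of -0.65 lies inside the prespecified margin, so such a claim is not a type I error. At the boundary of -0.7 the rate is 2.5% with a two-sided 95% CI. Calling 4.3% an inflation assumes that 0.65 is already the margin.
- A reader might infer that a lower limit between -0.70 and -0.65 would violate the decision rule. It would satisfy it. The conflict is with the stated derivation of the threshold.

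**Conclusion.** The point holds in limited form. The margin is misdescribed: it is 53.8% of the smallest MID, not 50%, through an undisclosed rounding in the lenient direction, and the value carries into the primary decision rule. The inference from the placebo-effect guideline is unsupported, and compliance with that guideline is indeterminate.

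The size is 0.05 PSFS points. For the planned 312, moving to 0.65 lowers power from 92.2% to 88.1% on the baseline-adjusted 95% CI basis, or from 90.0% to 85.9% on the basis that reproduces 312. These figures assume a true difference of 0, SD 2.0, 10% loss, 140 analysed per arm and, for the adjusted basis, a correlation of 0.5. The severity is moderate to minor, because the threshold is unambiguous and consistently applied.

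**What to change.** Set the margin to 0.65 wherever it appears in Sample size and Primary analysis, and restate the power for 312 randomised with its basis: about 88% with baseline adjustment at a correlation of 0.5 and a two-sided 95% CI, or about 86% on the one-sided 5%, SD 2.0 formula. Make the change before outcomes are compared by arm. A tighter margin is conservative.

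If the investigators prefer to keep 0.7, they should state that 0.65 was rounded up and that 0.7 is about 54% of the smallest reported MID.

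In either case, present the margin as a clinical-acceptability margin based on the smallest reported MID, and remove the inference from the guideline on the standard-care-versus-placebo effect.

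The cost is wording and, with 0.65, a stated power slightly below 90%, with no extra patients. Only if 90% must be held at 0.65 does the total rise, to 334 on the adjusted 95% CI basis or 363–364 on the formula behind 312.

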### Blinding

The participants, therapists and assessors will not be blinded. The surveys administered during this trial are self-assessments completed by patients directly in REDCap who will be blinded to the study hypothesis. If required, an independent blinded assessor may contact the patient to assist them with completing their surveys.

### Data collection methods

Patients will receive a unique link via email or phone message to complete all their surveys directly in REDCap. Patients will receive an email or phone message 2 days prior to each milestone, reminding them to complete their respective surveys. Two reminders followed by a phone call will be provided to patients who do not complete their surveys by the respective milestone. The treating clinicians may remind the participants to complete their surveys during their routine clinical reviews. The clinicians will not be able to complete, nor alter the results from the surveys. If requested, paper copies of the surveys may be sent to participants with their responses transcribed verbatim into REDCap by an independent blinded assessor not involved in this study.

### Data management

All study data will be collected, logged and stored within SLHD’s REDCap server. REDCap functions such as adding a field note (a brief descriptor of the question or answer), autocalculations and using data validation functions will be used to ensure data quality. The ‘required’ field is also used to ensure participants complete the mandatory questions prior to submitting the survey. The questionnaires will be tested by clinicians and patients prior to implementation. The research team will have access through a personal login and password.

### Statistical methods

An intention-to-treat analysis will be implemented after the database is cleaned and locked. Separate analyses will be conducted on each outcome. Descriptive statistics will be used for patient demographics and clinical characteristics. Categorical variables will be described with frequencies (%), and continuous variables will be described with means and SD. Data will be analysed using STATA V.14 statistical software (StataCorp) or R V.4.2.1 (R Foundation for Statistical Computing, Vienna, Austria. https://www.R-project.org/).

### Primary analysis

Non-inferiority trials assess whether an intervention outcome is not clinically worse than a control. The PSFS score at 12 weeks post-randomisation is the primary outcome in this study and we have prospectively defined a non-inferiority margin (ΔT) of −0.7 points, which is the maximum difference we are prepared to tolerate and still consider virtual care not to be clinically inferior to in-person care. The null hypothesis is, therefore, that a difference of greater than ΔT exists in favour of in-person care (H0: Δ ≤−ΔT). This will be assessed by creating a 95% CI, which should be entirely above the non-inferiority margin for the intervention to be declared non-inferior. The PSFS score will be compared between treatment groups as the dependent variable in a generalised linear regression model for the primary analysis adjusting for baseline PSFS variables. The treatment difference will be based on the estimate of adjusted means and 95% CIs.

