People with any type of simple fracture that is deemed appropriate for virtual care will be eligible for the trial, to reflect usual practice. The most common types of fracture are expected to be base of fifth metatarsal, ankle Weber A, and Mason I radial head. Uncommon types of simple fracture could include greater tuberosity or clavicle. Patients who consent to participate and complete their baseline measures will be enrolled in this study. Informed consent (online supplemental file 1) and study data will be collected and managed using the Research Electronic Data Capture (REDCap) tool hosted at SLHD.^11 12^ The randomisation schedule will be computer-generated using REDCap’s randomisation model and will be stratified in random blocks of 4, 6, 8 and 10 to ensure equal numbers in both groups and concealed allocation. A biostatistician not involved in this study will set up the allocation schedule and upload it into REDCap. Only the biostatistician will be aware of the allocation to ensure concealment. The study coordinator will randomise the patients to the study groups. Participants randomised to the VFC who agree to participate in the qualitative substudy will be purposively selected for an interview according to their age, employment status, tertiary education level, type of injury and discharge status. Selected participants will be contacted once they are discharged from the clinic to ensure their complete experience with the VFC is captured.

10.1136/bmjopen-2023-080800.supp1Supplementary data

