#### Secondary analysis

Secondary clinical outcomes will be analysed using logistic regression for binary outcomes and linear regression for continuous outcomes. Results from the analyses will be presented as point estimates with 95% CIs. Baseline scores will be included in the model to increase statistical precision. If more than 5% of data are missing, then imputation techniques may be considered.

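### The primary model adjusts only for baseline PSFS; prespecifying fracture region, age and baseline pain would modestly narrow the interval that decides non-inferiority

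*Protocol article*

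**What the plan says.** The Primary analysis section of the protocol article compares 12-week PSFS between arms in a "generalised linear regression model for the primary analysis adjusting for baseline PSFS variables". The 95% CI for the adjusted difference must lie wholly above −0.7. The plural in that phrase may cover more than one PSFS quantity, but nothing outside the PSFS is named.

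The Eligibility criteria section admits any simple fracture suited to virtual care: "The most common types of fracture are expected to be base of fifth metatarsal, ankle Weber A, and Mason I radial head". Shoulder and clavicle fractures are expected less often. The inclusion criteria set an age limit and require imaging that confirms the injury. Table 1 lists pain NRS and patient characteristics at baseline, and enrolment requires completed baseline measures.

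For secondary outcomes, the Secondary analysis section gives the reason for adjustment: "Baseline scores will be included in the model to increase statistical precision".

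The Sample size section states: "A total sample of 312 participants will provide 90% power to detect a non-inferiority margin of 0.7 points". The total allows for one participant in ten being lost. The other inputs given there are "an SD of 2.0, α of 5% and a correlation score between baseline and final scores of 0.5 at 12 weeks".

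**The concern.** In a linear model for a continuous outcome, any baseline variable that predicts the outcome and is left out stays in the residual variance and widens the interval for the treatment effect. Here that interval is the decision rule. Patients with foot, ankle, elbow and shoulder injuries may well differ in how far they have recovered at 12 weeks, and age and initial pain are natural further predictors. The article accepts precision as a reason to adjust, but applies it only to the baseline value of the outcome itself.

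At stake is some avoidable width in the interval compared with −0.7, and some protection if baseline PSFS predicts 12-week PSFS less well than planned. The latter is plausible, because each patient chooses the tasks that are scored.

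**Working it through.** **Inputs from the Sample size section:** N = 312, 10% loss, SD 2.0, baseline–final correlation ρ = 0.5, margin 0.7, power 90%. True difference taken as 0. **Decision rule from Primary analysis:** 95% CI, that is, one-sided 2.5%. **Assumed, not in the document:** the share R² of the variance remaining after baseline PSFS that region, age and pain explain.

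**Step 1. The plan's own figure.** Per arm, n = 2 × SD² × (z_α + z_β)² / margin². With one-sided 5% and SD 2.0: 2 × 4 × (1.645 + 1.282)² / 0.49 = 139.8, so 140 per arm, 280 in all, and 280 / 0.9 = 311.1, so 312. The stated total is reproduced. It uses the unreduced SD, so baseline adjustment is not what produces 312. With the residual SD from adjustment and one-sided 2.5%, the same formula gives 129 per arm, 258 in all, and 287 after loss.

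**Step 2. The planned model under the 95% CI rule.** Residual SD = 2.0 × √(1 − 0.25) = 1.732. With 280 analysed, SE = 1.732 × 2 / √280 = 0.207 and the half-width is 1.96 × 0.207 = 0.406. For power, use the unrounded 312 × 0.9 = 280.8 (140.4 per arm): SE = 0.2067, and Φ(0.7 / 0.2067 − 1.96) = Φ(1.43) = 92.3%.

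**Step 3. Adding covariates.** The SE is multiplied by √(1 − R²). The equivalent gain in analysed participants is 280 / (1 − R²) − 280.

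| Assumed R² | CI half-width | Power | Equivalent extra participants |
|---|---|---|---|
| 0 | 0.406 | 92.3% | 0 |
| 0.02 | 0.402 | 92.8% | 6 |
| 0.05 | 0.395 | 93.5% | 15 |
| 0.10 | 0.385 | 94.6% | 31 |

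**Step 4. Cost of three extra parameters.** Residual degrees of freedom fall from 280 − 3 = 277 to 274. If the covariates predicted nothing, the half-width would grow by a factor of about √(277 / 274) = 1.005, to about 0.408. The table ignores this small cost. Break-even is near R² = 3 / 277, about 1%.

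**Step 5. A weaker baseline correlation.** The same power formula with residual SD = 2.0 × √(1 − ρ²) × √(1 − R²):

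| ρ | R² = 0 | R² = 0.05 | R² = 0.10 |
|---|---|---|---|
| 0.5 | 92.3% | 93.5% | 94.6% |
| 0.4 | 89.2% | 90.7% | 92.1% |
| 0.3 | 86.7% | 88.4% | 90.0% |
| 0 | 83.5% | 85.3% | 87.1% |

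**The case against.** The strongest reply is that nothing here is wrong. Baseline-adjusted linear regression is a sound primary analysis, further covariates are often left to an analysis plan, and the one for this trial is not shown. At the protocol's own inputs the model exceeds its 90% target, and at R² = 0.10 the half-width shrinks by only 0.406 − 0.385 = 0.021 points, 3% of the margin. All of that stands, and it limits the point to an efficiency gain. It does not remove the point, because the article itself fixes the model that decides the trial.

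A reader might infer more than the document supports:

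- *That the estimate is biased or the error rate inflated.* Under randomisation with a linear model, neither follows.
- *That chance imbalance in fracture region is a second harm.* It is the same variance seen from another side. Suppose limbs split evenly and differ by 1.5 points. The 95% range of the imbalance is 1.96 × √(0.25 × 4 / 280) = 0.117, which shifts the estimate by up to 0.176. Region then contributes 1.5² / 4 = 0.5625, or 19% of the residual variance of 3.0. Removing it gives 0.406 × √(1 − 0.1875) = 0.366, and √(0.406² − 0.176²) is also 0.366. The interval already covers it.
- *That baseline PSFS cannot reflect regional differences.* Each task is scored against the patient's own pre-injury ability, which may absorb part of them.
- *That randomisation leaves fracture region unbalanced by design.* The article calls the randomisation stratified but names no factor, so this is unknown.

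Age and injury type must be known from the eligibility criteria, but the baseline characteristics are not itemised, so a coded region variable is inferred.

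**Conclusion.** The point holds as a modest, low-cost improvement to a valid analysis, not as an error or contradiction. For an assumed R² of 0.02 to 0.10, the half-width falls from 0.406 to between 0.402 and 0.385, and power rises from about 92% by roughly 0.5 to 2 points. At the low end of that range, the three extra parameters take back about half the gain. The stronger argument is insurance: under the 95% CI rule, power with baseline PSFS alone falls below 90% at a correlation of 0.4 (89.2%) and to 86.7% at 0.3, where an R² of 0.10 brings it back to 90.0%. All of this rests on a true difference of zero, an SD of 2.0, 10% loss, and a prognostic strength that the document does not give.

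**What to change.** In the Primary analysis section, prespecify before any outcome is seen a linear model for 12-week PSFS with arm, baseline PSFS, fracture region (upper or lower limb), age and baseline pain NRS. Keep the model with baseline PSFS only as a sensitivity analysis. If the analysis plan already names such covariates, the two documents need only be aligned.

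The cost is one sentence and three degrees of freedom out of about 277. These variables should be available before randomisation and enrolment requires completed baseline measures, so no participant should be lost; confirm that fracture region is coded at baseline.

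Do not carry the covariates over to binary secondary outcomes that may be rare, such as surgery or emergency re-presentation. In logistic regression, extra covariates risk sparse-data problems when events are few and change the odds ratio being estimated.
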